#### Relationship, ART Adherence, and Biomedical Measures

In this study, we will assess the feasibility of collecting behavioral and biomedical measures and provide a preliminary understanding of outcomes. The SOAR intervention is designed to provide transgender women skills in assessing disclosure and related risks, and association communication skills to discuss HIV with partners. We will administer surveys for relationship satisfaction [63] and communication [64], HIV disclosure [65], and HIV treatment adherence [66] Also, we will assess HIV viral load using whole blood. All measures will be administered at baseline through follow-up.

All data will be analyzed using similar procedures as outlined in aim 1 of this study.

#### Participants

For both study aims, all transgender women will be over the age of 18 years, be in a relationship for more than a month, own a smartphone, be comfortable with group discussions about HIV, and be HIV-positive with confirmatory testing using OraQuick (OraSure Technologies) during screening. We will enroll with racial diversity to ensure the representation of multiple voices. Our relationship criteria require participants to have a self-reported romantic or emotionally connected partnership with another individual of any sex or gender, and partners must be either HIV-negative or of unknown status. Additionally, all participants need to live in Eastern Cape and suboptimally adhere to their HIV treatment [66].

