### Procedures

#### Overview

Once enrolled, participants will complete a behavioral survey on REDCap. These measures cover HIV, sexuality, relationship stigma and discrimination, communication in relationships, and HIV prevention and treatment behaviors [47-53]. They will also complete syphilis testing using a rapid diagnostic test (Abbott Determine Syphilis TP), blood draw for HIV viral load, and urine collection for *Chlamydia trachomatis* and *Neisseria gonorrhea* testing. All measures will be administered by study staff.

Afterward, participants will receive training in Zoom, and their smartphones will be assessed and set up for Zoom compatibility. Participants will be notified that they will receive an SMS reminder 12 hours before each session, and then 1 hour before each session, they will receive an SMS with the Zoom link for that session. Also, participants will be informed that during the intervention they will be asked to complete an action plan, and they will receive a partner referral letter via SMS or in paper form (their choice) at the start of the study and can request the letter throughout the study. The referral letter describes the availability of local HIV and mental health services. Each participant will be informed that they will complete 1 SOAR session per week for 5 weeks with 2 check-in sessions afterward.

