### Limitations

The one potential study limitation is smartphone ownership or access. Specifically, although smartphone use is high in South Africa, device costs may be prohibitive for some participants. To facilitate participation such that we have representation of transgender women across socioeconomic standing, we will provide smartphones for participants to borrow, or they may access a tablet with headphones at a community site to attend the sessions.

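### Smartphone ownership is an entry criterion, yet the Limitations section promises loan devices for women who cannot afford one; read literally, the criterion excludes the women the loans are meant for.

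*Protocol article*

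**What the plan says.** The Participants section gives one list of criteria for the whole study, opening with "For both study aims, all transgender women will be over the age of 18 years". The list includes the requirement to "own a smartphone, be comfortable with group discussions about HIV". It offers no alternative such as access to a shared or borrowed device.

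The Limitations section begins "The one potential study limitation is smartphone ownership or access". It explains that "although smartphone use is high in South Africa, device costs may be prohibitive for some participants" and states its aim: "To facilitate participation such that we have representation of transgender women across socioeconomic standing". The measure follows: "we will provide smartphones for participants to borrow, or they may access a tablet with headphones at a community site to attend the sessions".

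The Procedures overview describes device set-up after enrolment: "their smartphones will be assessed and set up for Zoom compatibility". It mentions no step for issuing a loan device.

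**The concern.** The two sections appear to describe different populations. Under the entry criterion, a woman who has no smartphone because she cannot afford one is ineligible. Under the Limitations text, she is the person for whom the study will supply a device.

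This matters because feasibility is the question of aim 2. The Feasibility section defines it through recruitment, retention, message exchange and engagement in group sessions, and device access bears on each. Expected Findings makes an efficacy study conditional on videoconference delivery proving feasible for transgender women. If only owners could enter, that conclusion says nothing direct about women without a phone. The criterion also covers aim 1, so the interviews on videoconference delivery preferences would come from owners too.

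**Working it through.** The check compares texts. There is no planned figure to reproduce and no formula to apply.

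1. **Scope of the rule.** The Participants section applies its list to both aims. The recruitment paragraphs for aim 1 (Tailoring SOAR for Transgender Women) and aim 2 (Evaluating the Feasibility of SOAR for Transgender Women) say nothing about devices, so the Participants section alone sets the device rule.

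2. **Content of the rule.** The verb is to own. Nothing elsewhere in the article waives this or says that a borrowed device satisfies it.

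3. **Target of the loan measure.** The Limitations section gives three reasons for it: ownership or access, cost ("device costs may be prohibitive for some participants"), and representation of women in all economic circumstances. All three point to women who lack a device.

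4. **Order of events.** Screening comes before enrolment, and set-up comes after it. A woman without a smartphone fails at screening and never becomes a participant who could borrow one.

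5. **Procedures.** The overview speaks of the participants' own phones being prepared for Zoom. This fits the owners-only reading and does not describe the loan route.

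6. **Size.** If a share p of otherwise eligible women had no smartphone, literal use of the criterion would turn away 20 × p of every 20 such women approached. The article gives no value for p, so the count cannot be worked out. Its general remarks in the Introduction, Expected Findings and Limitations describe smartphone use as high or established, so p may be small.

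7. **What a repair must respect.** Several procedures assume a participant's own phone number. Usability Testing sends reminders, self-assessments, action plans and partner referrals to smartphone numbers. The Procedures overview and Group Check-Ins send Zoom links or connection details by SMS. Retention Procedures confirms numbers by SMS each month. A tablet at a community site does not obviously receive any of these, so changing the eligibility phrase alone would leave a gap.

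**The case against.** The strongest defence is that the loans serve enrolled owners whose phone turns out to be incompatible, broken or lost. The overview does check each phone for Zoom after enrolment, and Retention Procedures foresees technical difficulties in sessions. A reader might infer from the conflict that the loan measure could never operate and that nobody in the sample would use it. The documents do not support that: an owner with an unusable phone could borrow one under the Limitations wording. But this use does not resolve the conflict, because the reasons given for the measure are ownership, cost and economic representation, not equipment failure.

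A second defence is that staff may have worked to the Limitations text and enrolled women who borrowed devices. The article does not show how screening was done, so this is possible. A reader might therefore go too far in stating that feasibility and acceptability are biased upward. That depends on which rule governed. Even under the owners-only rule, it is conjecture that borrowers would attend less: a woman lent a phone and given the study data plan has her device barrier removed. Nor does the article give grounds to think that satisfaction ratings would be inflated. What can be said is that an owners-only sample gives no direct evidence about women without a phone.

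Third, the pilot is finished, so no change of wording alters who was enrolled. This is correct. It limits the remedy for this sample to reporting, but leaves the criterion open to correction before a later trial.

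Finally, an article may leave much detail to a fuller protocol. That does not help here, because the article itself states both rules and they conflict.

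**Conclusion.** The conflict is real and should be corrected. As written, the entry criterion excludes the women the loan measure is meant to include. If it was applied literally, the stated economic representation was not achieved, and the feasibility conclusion covers smartphone owners only.

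The size is unknown. The article gives neither an ownership rate nor any account of screening, so exclusion is what the criteria imply and not an observed event. The pilot planned 20 women, and the Results section reports 14 who completed between one and five sessions. A reader might link that shortfall to the device rule, but the documents give no reason for it and do not support the link.

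The consequence is for the population to which the feasibility finding applies and for how recruitment is interpreted. No hypothesis test or sample size changes.

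**What to change.** Reconcile the Participants and Limitations sections, and the set-up text in the Procedures overview. There are two ways to do it:

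- **Preferred:** change the criterion to 'own, or be willing to use a study-provided, smartphone or tablet'. Add a loan step to set-up, and state how a tablet user will receive the session links, reminders and other material now sent by SMS to a participant's phone.
- **Alternative:** keep the ownership criterion, withdraw the representation claim in Limitations, and limit the feasibility conclusion to smartphone owners.

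For the completed pilot, state which rule was applied at screening. Where the records allow, report how many women used a borrowed device and how many were screened out for lack of one. Carry the corrected criterion into the planned efficacy trial.

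The cost is small. The article already promises the devices, so the work is an eligibility phrase, a loan step, a message route for tablet users and a few lines of reporting. The downside is that borrowed devices or a shared site may bring some attendance or privacy problems that an owners-only sample would not show. In a feasibility study, those are worth seeing.

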### Ethical Considerations

For this study, aim 1 procedures have been reviewed and approved by the University of Cape Town Review Board (FWA00001938) with reliance on the institutional review board at Arizona State University (STUDY00014539). For aim 2, the study procedures were reviewed and approved by the University of Pretoria Review Board (189/2022) with reliance on Arizona State University (16397). All participants completed written informed consent. All participants will complete written informed consent and will receive R150 (around US $10) as travel reimbursement for completing the study activities and an R150 (around US $10) data plan to support their session attendance. All data will be anonymized when reported.

## Results

Staff hiring and intervention tailoring began in May 2023 and were completed in November 2023. During this time, interviews were completed and we identified preferences for the integration of gender-affirming care and South African transgender women’s voices (eg, videos) into SOAR sessions. Feasibility pilot testing started in January 2024 and was completed in January 2025. At this time, there are 14 participants who have completed 1-5 SOAR sessions. Primary feasibility results will be used to inform further adaptation and a clinical trial.

## Discussion

### Expected Findings

The SOAR intervention for transgender women is responsive to South African clinical guidelines for HIV care and addresses barriers to HIV disclosure management and treatment with partners [67]. Specifically, recent clinical guidelines outline a recommendation to deploy mHealth tools for treatment support, as these may allow transgender women to navigate perceived and enacted stigma and discrimination more easily when seeking clinic care [15,16]. Given the established smartphone use in South Africa, and among transgender women, harnessing these tools in HIV interventions is feasible [68]. However, few mHealth HIV interventions have been designed and tested for transgender women [4].

SOAR leverages videoconferencing and group format for delivery. Both modes of delivery have been shown to be highly effective in other settings [69,70], and more research is needed to determine its feasibility with transgender women in South Africa. Further, SOAR has the potential to improve skill-building for HIV status disclosure management that may in turn garner needed support from partners and improve HIV treatment adherence. If partner disclosure and support are not feasible, then SOAR provides participants with coping skills to manage HIV treatment and identification of other support systems for care.

Given that transgender women have some of the highest HIV incidence rates in South Africa and globally [4], it is imperative that we develop more intervention options based on their lived experiences. Integrating mHealth tools into these interventions can empower participants, as it allows them to control engagement based on their safety and needs. If SOAR is feasible as videoconference delivery for transgender women, then we will propose an efficacy study of the intervention to understand the impact on HIV viral load and quality of life. The intervention has the potential to build relationship skills around HIV treatment for transgender women and their partners who are consistently left behind in the HIV response.

### Limitations

The one potential study limitation is smartphone ownership or access. Specifically, although smartphone use is high in South Africa, device costs may be prohibitive for some participants. To facilitate participation such that we have representation of transgender women across socioeconomic standing, we will provide smartphones for participants to borrow, or they may access a tablet with headphones at a community site to attend the sessions.

## Abbreviations

ART: antiretroviral therapy
HR: Healthy Relationships
IDI: in-depth interview
PrEP: pre-exposure prophylaxis
REDCap: Research Electronic Data Capture
SOAR: Speaking Out and Allying Relationships
